#### 8.3.5 Adverse Event Reporting

All **Adverse Events (AEs)** that occur during the trial will be documented in the patient's medical history. AEs that were related with the study medications (AR and SAR) or not related but serious (SAE) will be collected on the appropriate page of the eCRF, the following information about the AEs will be recorded: description, start and end date, severity, seriousness, evaluation in relation to the investigation drug, actions taken and outcome.

Any pre-existent illness exacerbation that occurs after drug study initiation should be considered as an adverse event.

Any abnormal lab result that the investigator considers clinically important and that requires study drug dose adjustment, transitory or permanent study drug discontinuation or any other interventional measure or diagnostic evaluation for patient risk evaluation will be collected as an adverse event and should be investigated and monitored appropriately.

**Serious Adverse Reaction (SAR)** that occur during the trial must be **notified to the sponsor** within a maximum period of 24 hours from the time of knowing about the event.

Also, the investigator shall complete and sign the SAR report form and send it by fax or email to:

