## 6.2 CONCOMITANT THERAPY

There is no specified 'per-protocol' concomitant medication or treatment. Any drugs other than those listed in section 6.3.2 are allowed, and should be administered, as necessary for the treatment of the patient. Only concomitant cardiovascular treatments, such as other catecholamines, hydrocortisone or others, should be documented on the appropriate eCRF. Fluid boluses are considered also cardiovascular treatment and should be recorded on the eCRF.

All allowed medications that have been started before screening may be continued during the study. Medications for treatment of emerging illnesses that arise after screening will be allowed. The medication and the condition must be documented on the adverse event page of the eCRF (when applicable, please refer to the assessment of safety section of the protocol). For any concomitant therapy given as a treatment for a new condition or a worsening of an existing condition, the condition must be documented on the adverse event page of the eCRF (when applicable, please refer to the assessment of safety section of the protocol).

---

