### 6.2.1 Rescue Treatment

A change in treatment strategy using rescue treatments is allowed if no clinical response to the study intervention is considered by the attending physician, when the

- MABP < GA-5 mmHg
- and one or more of the following:
- SVC flow < 51 ml/kg/min (after 1 hour)
  - Rising serum lactate
  - Base excess being more negative
  - CRT ≥ 4sec

Rescue treatments include:

- Additional fluid bolus
- vasopressor-inotrope therapy, apart from commercial dobutamine
- corticosteroids
- other treatment administered to treat haemodynamic insufficiency

When rescue treatment is needed physicians will be encouraged to consider up-titration option first, to try to maintain the infant in the study drug only treatment corridor as long as possible, if it is the best option for the infant. Rescue treatment will not include commercial dobutamine.

---

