## 8.3 ADVERSE EVENTS AND SERIOUS ADVERSE EVENTS

### 8.3.1 Definition of Adverse Events (AE)

#### **Adverse Event (AE):**

Any untoward medical occurrence in a patient or clinical investigation patients administered a medicinal product, which does not necessarily have a causal relationship with this treatment (the study medication).

An AE can therefore be any unfavourable and unintended sign (including an abnormal laboratory finding), symptom or disease temporally associated with the use of the study medication/procedure, whether considered related to the study medication.

This includes any newly occurring event, or a previous condition that has increased in severity or frequency since the administration of study drug.

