#### 8.3.3.2 Relationship to Study INTERVENTION

All adverse events (AEs) must have their relationship to study intervention assessed by the clinician who examines and evaluates the participant based on temporal relationship and his/her clinical judgment. The degree of certainty about causality will be graded using the categories below. In a clinical trial, the study product must always be suspect.

- **Related** – The AE is known to occur with the study intervention, there is a reasonable possibility that the study intervention caused the AE, or there is a temporal relationship between the study intervention and event. Reasonable possibility means that there is evidence to suggest a causal relationship between the study intervention and the AE.
- **Not Related** – There is not a reasonable possibility that the administration of the study intervention caused the event, there is no temporal relationship between the study intervention and event onset, or an alternate etiology has been established.

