#### Safety:

Safety analysis will be conducted for the whole study population as well as for the five treatment groups separately. AEs and SAEs will be reported with absolute and relative frequencies per treatment group along with the corresponding 95% CIs (two-sided). Differences between different groups (each of the dose regimens separately) will be compared using Chi-squared Test. For all comparisons 95% CIs (two-sided) will be provided.

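### Worsening of the condition under study counts as an adverse event and is not separated in the by-dose safety comparison, so lack of efficacy at low doses could flatten or reverse the AE table

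*Protocol*

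**What the plan says.** Section 8.3.1 includes in its AE definition "a previous condition that has increased in severity or frequency since the administration of study drug". Section 8.3.5 repeats this more broadly: "Any pre-existent illness exacerbation that occurs after drug study initiation should be considered as an adverse event". It adds a laboratory rule, "Any abnormal lab result that the investigator considers clinically important and that requires study drug dose adjustment", which also extends to other interventions and to diagnostic work-up. Neither section excepts the haemodynamic insufficiency that is the entry criterion in 5.1.

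The laboratory values concerned also measure efficacy. Section 8.1.1.4 lists falling lactate and improving base excess among the parameters checked at dose evaluation. Section 6.2.1 lists "Rising serum lactate" and worsening base excess among the criteria for rescue, and both 6.1.2 and 6.2.1 encourage up-titration as the first step.

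On what is recorded, 8.3.4 and 8.3.5 send to the eCRF only events that are related to study drug, or that are unrelated but serious. Under 8.3.3.2, one alternative sufficient for a related event is that "there is a temporal relationship between the study intervention and event". Section 6.2 adds, with a pointer to the safety section, that where therapy is given for "a worsening of an existing condition, the condition must be documented on the adverse event page of the eCRF".

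Section 9.1.2 (Safety) reports AEs and SAEs per treatment group and states: "Differences between different groups (each of the dose regimens separately) will be compared using Chi-squared Test". It does not restrict this by causality and does not separate worsening of the study condition.

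**The concern.** The same episode can be read twice. An infant on the allocated dose whose lactate rises, and whose dose is increased for that reason, is a failed response in the efficacy data. If the investigator judges the result clinically important, the infant also has an AE. Deterioration that is fatal or life-threatening is an SAE and is collected whatever its cause.

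The protocol expects failure to be most frequent at the lowest dose, whereas dose-related toxicity would be expected to rise with dose. Mixing the two in one count pulls the by-dose AE rates in the opposite direction to true toxicity. What is at stake is a stated secondary endpoint, the comparison of AE and SAE frequencies between dose groups in a dose-finding trial.

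**Working it through.** **Inputs from the protocol (section 9.1.1).** Efficacy by dose is 45/70/80/90/95% at 5/7.5/10/12.5/15 microg/kg/min. Expected patients are 5/9/12/4/0, with a maximum of 30.

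**Check of the plan's figures.** 5 + 9 + 12 + 4 + 0 = 30, as stated. A continual reassessment simulation gave 3.4/8.4/13.2/4.9/0.1 patients, each within 2 of the plan. It used the power model, the stated efficacies as both prior and truth, target 80% and cohorts of 3. Starting at the lowest dose, no skipping and prior variance 1.34 were assumptions. A tighter prior (SD 0.5) gave 3.0/6.2/17.9/2.9/0.0. The steps below use the printed numbers.

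**Implied non-response, q = 1 − efficacy.** 55/30/20/10/5%. Expected non-responders are 5(0.55) + 9(0.30) + 12(0.20) + 4(0.10) + 0 = 2.75 + 2.70 + 2.40 + 0.40 = 8.25 of 30.

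**Model.** Two quantities are not in the protocol and are assumed: t, the true toxicity rate at each dose, and f, the share of non-responders who have worsening or a qualifying laboratory result recorded as an AE. With the two sources independent within dose,

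AE rate = 1 − (1 − t)(1 − f·q).

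With t = 5/10/15/20/25%:

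| f | 5 | 7.5 | 10 | 12.5 | 15 |
|---|---|---|---|---|---|
| 0 | 5% | 10% | 15% | 20% | 25% |
| 0.3 | 21% | 18% | 20% | 22% | 26% |
| 0.5 | 31% | 23.5% | 23.5% | 24% | 27% |
| 1 | 57% | 37% | 32% | 28% | 29% |

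For example, at 5 microg/kg/min with f = 0.5: 1 − 0.95 × (1 − 0.5 × 0.55) = 1 − 0.95 × 0.725 = 0.311.

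**Where the order of 5 and 12.5 reverses.** Setting the two rates equal gives f* = (t₁₂.₅ − t₅) / [(1 − t₅)q₅ − (1 − t₁₂.₅)q₁₂.₅].

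- Toxicity 5–25%: 0.15 / (0.95 × 0.55 − 0.80 × 0.10) = 0.15 / 0.4425 = 0.34.
- Toxicity 5–20% (16.25% at 12.5): 0.1125 / (0.5225 − 0.08375) = 0.1125 / 0.43875 = 0.26.
- Toxicity 5–35% (27.5% at 12.5): 0.225 / (0.5225 − 0.0725) = 0.225 / 0.45 = 0.50.
- Toxicity flat at 5%: any f above 0 creates a false downward gradient. At f = 0.5 the rates are 31/19/15/10/7%.

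The upper ends of the stated prior ranges (non-response 50% and 5%) barely change the first result: 0.15 / (0.475 − 0.04) = 0.34. In patients, f = 0.34 at the lowest dose is 0.34 × 2.75 = 0.9, about one infant.

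**Chance of a misleading table (toxicity 5–20%, planned numbers, exact binomial).** The probability that 5 shows a higher observed AE rate than 10 (n = 5 and 12) is 19% at f = 0, 65% at f = 0.5 and 84% at f = 1. For 5 against 12.5 (n = 5 and 4) it is 12%, 57% and 84%.

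**The test itself.** For 55% against 20% with 5 and 12 infants, power is about 30% by normal approximation. The risk is therefore a misread table more than a false significant result.

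**The case against.** The strongest reply is that the quoted sentence is ordinary AE wording and is not wrong in itself. That stands. The weakness lies in its combination with the relatedness rule and the unrestricted comparison.

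Two filters also stand in part. Non-serious unrelated events do not reach the eCRF, and 8.3.3.2 allows an event to be called unrelated when another cause is established, which progression of the presenting illness may be. Section 6.2 refers back to the safety section and so is not a fully independent route to the AE page. These filters remove some events but not reliably, since timing alone can make an event related and serious worsening is kept regardless of cause.

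A reader might infer more than the documents support:

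- *Every non-response is an AE.* It is not. An infant whose SVC flow rises from 45 to 53 ml/kg/min has missed the response criterion but improved. The text needs an exacerbation, or a laboratory result that is abnormal, judged clinically important and followed by action. The 55/30/20/10/5% figures are therefore not AE rates.
- *Failure is counted as toxicity.* An AE in 8.3.1 need not be caused by the drug, and causality is graded separately.
- *Dose-finding is distorted.* Allocation in 6.1.1 uses therapeutic response only, and the alerts in 6.1.3 use only heart rate and blood pressure.

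It can also be said that a separate table line belongs in a statistical analysis plan, which is not shown. In part it does. But the AE rule, the relatedness rule and the comparison are fixed in the protocol. Without a flag at collection, events would have to be reclassified afterwards in a trial where the dose is known.

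Finally, f and the toxicity gradient are assumed, and the model ties events to the allocated dose although non-responders may be up-titrated. Even at f = 0 the small groups misorder 5 and 10 in 19% of trials.

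**Conclusion.** The concern holds in limited form. The protocol defines AEs so that worsening of the study condition, and lactate or base excess changes that prompt action, can enter the safety counts. It then compares those counts between doses without setting them apart. On its own efficacy figures such events would be concentrated at low doses.

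The direction follows from the document; the size does not. The 5 against 12.5 order reverses once the recorded share of non-responders passes roughly 0.26 to 0.50, for assumed toxicity rising from 5% to between 20% and 35% over the range. Below that share the gradient is flattened. The effect is confined to the secondary safety comparison, and with at most 30 infants it would show as a misleading table of rates. It is worth correcting because the remedy is small.

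**What to change.** Leave AE collection, causality grading and SAE reporting as they are. In 8.3.5, add an eCRF flag for worsening of the haemodynamic insufficiency under study, including lactate or base excess changes that the investigator judges only to reflect it. In 9.1.2, present by dose (a) all AEs and SAEs, (b) flagged worsening of the study condition, and (c) all other AEs and SAEs. State that (c) and the related events are used to read drug toxicity by dose, and that nothing is removed from (a).

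The flag should not be set automatically from the action taken, and flagged events should not be dropped from the comparison. The individual limits in 6.1.3 cover only high heart rate and high blood pressure, while 2.4.1 lists a fall in blood pressure among the known effects. A drug-induced fall followed by rescue could otherwise be labelled lack of efficacy and disappear from the comparison.

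The cost is one eCRF field, a few sentences and two extra table lines. Section 8.1.1.6 already asks investigators for a similar judgement on the cause of persistent circulatory failure. The drawback is one classification per event in an unblinded trial, which is why the all-event total stays in the table.

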## 9 STATISTICAL CONSIDERATIONS

### 9.1. STATISTICAL ANALYSES

#### 9.1.1. Analysis of the Primary Efficacy Endpoint(s)

To calculate the dose-escalated sample size, the Bayesian Method of Continual Reassessment (46-49) was used, using the following a priori probability of success for each dose:

- A. 5 mcg/kg/min → 45-50%
- B. 7.5 mcg/kg/min → 70-75%
- C. 10 mcg/kg/min → 80-85%
- D. 12.5 mcg/kg/min → 90-95%
- E. 15 mcg/kg/min → 95-100%

In addition, a target probability of 80%, maximum sample size of 30 patients and a confidence level of 90% was considered. The statistical software RStudio (version 4.1.1) and the web application of the Division of Translational Research and Applied Statistics, University of Virginia, were used.

Sample size: the estimated number of patients per dose is shown below:

|                        | STEP 1 | STEP 2 | STEP 3 | STEP 4 | STEP 5 |
|------------------------|--------|--------|--------|--------|--------|
| DOSAGE
(mcg/kg/min) | 5      | 7.5    | 10     | 12.5   | 15     |
| EFFICACY (%)           | 45     | 70     | 80     | 90     | 95     |
| PATIENTS (n)           | 5      | 9      | 12     | 4      | 0      |

After the simulation and at each dose-escalated, an implementation of the results obtained will be performed, recalculating the efficacy estimates per dose and the required number of patients. This escalation will stop when the expected efficacy is achieved.

#### 9.1.2. Analysis of the Secondary Endpoint(s)

Efficacy:

The proportion of infants who maintain an acceptable haemodynamic status with the dobutamine infusion alone in the first 72h from birth.

Patients with a loss of acceptable haemodynamic status in the first 72 h from birth, but with confirmation that the underlying aetiology of circulatory failure is different from transitional circulation adaptation will be excluded. These include sepsis, haemodynamically significant PDA, air trapping (lung over distension), pneumothorax, pleural or pericardial effusion

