| 
 
To determine the individual variables that explain the interindividual pharmacokinetic (PK)/PD variability.
 
 | 
 
To determine the correlation between PK and PD.
 
 
[A] The effective start of the infusion (t0) will be calculated as the time at which the infusion pump is switched on plus the empirical value for the interval arising from the dead space. We summarize t0 as “the time at which dobutamine is expected to reach the circulation”
 
[B] Acceptable haemodynamic status is defined, for the purposes of this study, as the achievement and maintenance of dose success during the first 72 h from birth. The loss of such acceptable haemodynamic status occurs whenever there is a change in therapeutic strategy that involves cardiovascular treatment other than dobutamine alone due to exceeded safety parameters, treatment failure of the investigational infusion or the need for rescue treatment or death; any additional fluid bolus is considered as cardiovascular treatment.
 |
|---------------------------------------------------------------------------------------------------------------------------------------------------------------|----------------------------------------------------------------------------------------------------------------------------------------------------------------------------------------------------------------------------------------------------------------------------------------------------------------------------------------------------------------------------------------------------------------------------------------------------------------------------------------------------------------------------------------------------------------------------------------------------------------------------------------------------------------------------------------------------------------------------------------------------------------------------------------------------------------------------------------------------------------------------------------------------------------------------------------------------------------------------------|

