## 6 STUDY INTERVENTION

### 6.1 STUDY INTERVENTION ADMINISTRATION

#### 6.1.1 Study Intervention Description

Once the patient has fulfilled the inclusion criteria, he or she will be allocated to a dosage regimen according by the study statistician. The statistician will be informed about the therapeutic response observed for re-estimation of the posterior probability of success after each cohort of 3 patients. The choice of allocation will be decided according to dose with the posterior probability closer to the target probability (80%).

The dobutamine solution is commercially available dobutamine (Dobutamine Generis, concentration 12.5 mg/mL). It will be impossible to blind carers or assessors to the dose used.

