#### 8.1.1.6 Efficacy Visit

To test whether dobutamine alone achieved and maintained an acceptable haemodynamic status during the first 72 h from birth (secondary objective).

This study short-term efficacy outcome means that at 72h the infant is alive, and the clinical condition is:

- SVC flow > 55 ml/kg/min;
- MABP > GA;
- Decreasing serum lactate levels;
- CRT < 4s;
- Urine output > 1 ml/kg/h;
- Dobutamine alone was used (regardless the dose).

Investigators will be asked to report if, according to this definition, short-term success has been achieved or not. If not, investigators will also be asked to check if persistent circulatory failure or death is due to something different from pure transitional circulation adaptation, e.g., sepsis, haemodynamically significant PDA, air trapping (lung over distension), pneumothorax, pleural or pericardiac effusion.

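### The 72-hour efficacy proportion drops infants only if they failed, so it overstates success on dobutamine alone whenever a failure is attributed to another cause

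*Protocol*

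**What the plan says.** Protocol section 9.1.2 names the secondary efficacy quantity: "The proportion of infants who maintain an acceptable haemodynamic status with the dobutamine infusion alone in the first 72h from birth". The exclusion that follows has two conditions. The first is the outcome: "Patients with a loss of acceptable haemodynamic status in the first 72 h from birth". The second is an attributed cause: "but with confirmation that the underlying aetiology of circulatory failure is different from transitional circulation adaptation will be excluded". Examples are given: "These include sepsis, haemodynamically significant PDA, air trapping (lung over distension), pneumothorax, pleural or pericardial effusion".

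Section 8.1.1.6 (Efficacy Visit) sets the order of events. The investigator first reports whether short-term success was achieved, and then: "If not, investigators will also be asked to check if persistent circulatory failure or death is due to something different from pure transitional circulation adaptation".

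Section 3, note [B], repeated in the synopsis, defines loss of acceptable status as a move to any cardiovascular support beyond dobutamine by itself. Apart from a breached safety limit, the note gives these triggers: "treatment failure of the investigational infusion or the need for rescue treatment or death; any additional fluid bolus is considered as cardiovascular treatment". It makes no exception for the cause of the loss.

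**The concern.** An infant can leave the denominator only by failing. A septic infant who holds an acceptable status to 72 hours counts as a success. A septic infant who dies or needs another cardiovascular treatment can disappear from the analysis. The cause is judged once the failure is known, and neither section 8.1.1.6 nor section 9.1.2 says what counts as confirmation.

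This proportion answers the first secondary objective and is the trial's 72-hour efficacy result. Section 2.2.3 places the trial on the path to a confirmatory phase III study. A success rate that can lose deaths from its denominator would give the planners of that study too favourable a figure.

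**Working it through.** **Inputs from the protocol**
- Maximum sample size 30 (section 9.1.1). The planned numbers per dose add up to it: 5 + 9 + 12 + 4 + 0 = 30.
- Only failures can be excluded (sections 9.1.2 and 8.1.1.6).
- The listed causes are not entry exclusions (section 5.2), so infants who have or develop these conditions can be in the trial.
- Section 7.1 refers to analysis of the whole intention-to-treat population. Section 7.2 removes from it only infants who never received the intervention.
- The protocol gives no expected value or precision for the 72-hour proportion, so there is no stated figure to reproduce.

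**Assumed:** the number of successes and the number of failures attributed to another cause. The documents give neither.

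**Step 1: against all treated infants.** Let N be the infants treated, S the successes and x the failures excluded. The written rule reports S/(N − x), and the all-treated proportion is S/N. The difference is

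S/(N − x) − S/N = S·x / [N(N − x)],

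which is positive whenever S > 0 and x > 0.

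**Step 2: against exclusion regardless of outcome.** Let s be the successes who have a listed diagnosis. Excluding them as well gives (S − s)/(N − x − s). The difference is

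S/(N − x) − (S − s)/(N − x − s) = s(N − x − S) / [(N − x)(N − x − s)].

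This is never negative. It is positive when at least one success has a listed diagnosis and at least one failure remains in the analysis. Enumerating the combinations for N = 30 found no violation of either inequality.

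**Step 3: illustration with N = 30.**

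| Successes | All treated | x = 1 | x = 3 | x = 6 |
|---|---|---|---|---|
| 15 | 50.0% | 51.7% | 55.6% | 62.5% |
| 18 | 60.0% | 62.1% | 66.7% | 75.0% |
| 21 | 70.0% | 72.4% | 77.8% | 87.5% |
| 24 | 80.0% | 82.8% | 88.9% | 100.0% |

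For example, 18/(30 − 3) = 18/27 = 66.7%. If 3 of the 18 successes had a listed diagnosis, exclusion regardless of outcome would give 15/24 = 62.5%.

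**Step 4: by share of failures removed.** With true success rate p and a share f of failures excluded, the reported rate is p/[p + (1 − p)(1 − f)].
- Smallest excess, p = 0.8 and f = 0.25: 0.80/0.95 = 84.2%, or 4.2 points.
- Middle, p = 0.6 and f = 0.5: 0.60/0.80 = 75%, or 15 points.
- Largest excess, p = 0.5 and f = 0.75: 0.50/0.625 = 80%, or 30 points.

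**Step 5: expected excess against both targets.** Let q be the share of infants with a listed cause. Let p now be the success rate without such a cause and r the rate with one. Suppose every failure with a listed cause is excluded and no other. The all-treated proportion is A = (1 − q)p + qr, the rule reports A/[1 − q(1 − r)], and the purely transitional proportion is p. With q = 0.2, p = 0.7 and r = 0.5, A = 0.66 and the rule reports 0.66/0.90 = 73.3%, against 66% for all treated and 70% for purely transitional infants. Over q = 0.1–0.3, p = 0.6–0.8 and r = 0.3–0.7, the excess is 1.9 to 17.3 points over all treated infants and 0.6 to 9.2 points over purely transitional infants.

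**The case against.** The strongest defence is that the restriction is deliberate. The trial concerns transitional circulation, section 8.1.1.6 names pure transitional adaptation as the condition of interest, and section 9.1.2 lists the other causes in advance and requires confirmation. Restricting to that population is a legitimate aim. What does not stand is the way it is done: a purely transitional estimate would also have to remove successes with the same diagnoses, and the rule keeps them.

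It is also fair that the quantity is a secondary, single-arm proportion with no hypothesis or success threshold attached, and that a statistical analysis plan not shown could add an analysis of all treated infants. That limits the consequences. It does not change what section 9.1.2 fixes.

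A reader might infer three stronger things that the documents do not support.
- **The dose-finding result is compromised.** It is not. The primary endpoint is superior vena cava flow at 1 and 3 hours, and allocation follows the therapeutic response observed after each cohort of 3. The 72-hour exclusion is not described as entering that process.
- **Comparison between dose groups is spoiled.** Section 9.1.2 plans no such comparison of this proportion, and section 8.1.1.6 counts dobutamine alone at any dose.
- **The open-label design causes the bias.** Section 6.1.1 does say "It will be impossible to blind carers or assessors to the dose used", but the problem is that the outcome is known when the cause is judged. It would remain if dose were blinded.

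**Conclusion.** The concern holds for the 72-hour secondary proportion. Against all treated infants the upward direction is certain once one failure is excluded and one infant succeeds. Against purely transitional infants the rule can never understate. It overstates when some success has a listed diagnosis and some failure remains. If no failure is attributed to another cause, there is no bias. The rule also contradicts the endpoint definition in section 3, which treats every loss or death as failure.

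The size rests on assumed inputs. At 18 successes in 30 it is about 2, 7 or 15 points for 1, 3 or 6 exclusions. Over true rates of 50–80% with 25–75% of failures removed it runs from about 4 to 30 points. The upper end comes only from the most extreme corner and should not be read as a forecast. Because the endpoint is secondary and separate from dose finding, this should be corrected, but it does not threaten the trial's main conclusion.

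**What to change.** In section 9.1.2, define the main 72-hour efficacy analysis on all infants who received dobutamine, and count every loss of acceptable status or death as failure whatever its cause. Report the attributed causes of failure descriptively. This agrees with note [B] in section 3.

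If a purely transitional estimate is wanted, present it as a sensitivity analysis that excludes every infant with a listed diagnosis, successes and failures alike, and state how each diagnosis is confirmed.

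The main change costs one paragraph and no new data; its price is a less favourable success figure. The sensitivity analysis is not free, because it needs the listed diagnoses recorded in successful infants too. Of these, section 8.1.2.1 lists only early infection and patent ductus arteriosus for all infants, and section 8.1.2.3 does not require ductal assessment at each echocardiogram. Air trapping, pneumothorax and effusions are not listed there and would need eCRF fields completed for every infant.
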